## Abstract

**Background:**

Silver diamine fluoride (SDF) is becoming more widely recognized as a simple, cost-effective approach to minimize sensitivity and arrest caries. However, SDF results in caries that are stained black. Potassium iodide (KI) treatment with SDF may minimize or lessen the staining. However, the effectiveness of KI on staining has not been investigated. Studies demonstrating that potassium iodide reduces the black staining are still insufficient. This paper presents the study protocol for Healthy Smiles, a randomized controlled trial implemented to compare the staining propensity of SDF and SDF+KI.

**Objective:**

This study, Healthy Smiles, aims to evaluate the staining propensity of SDF and SDF+KI using a Nix Mini color sensor among children aged 4 to 6 years. Another objective of the study is to evaluate the caries-arresting effect of SDF and SDF+KI in the treatment of carious primary teeth.

**Methods:**

This study is a randomized controlled trial. A total of 60 children with caries that meet the criteria of the International Caries Detection and Assessment System (code 1 or above) will be randomly assigned to treatment groups, where group 1 will be treated with SDF and group 2 will be treated with SDF+KI. Discoloration of treated lesions will be assessed digitally using a Nix Mini color sensor. Participants will be followed up at 1, 3, and 6 months after treatment to digitally record the ∆L and ∆E values using the Nix Mini color sensor. Data will be analyzed using SPSS (version 28; IBM Corp). Independent sample *t* tests and the Mann-Whitney *U* test will be used to compare the 2 groups.

**Results:**

Enrollment started in October 2023. It is estimated that the enrollment period will be 12 months. Data collection is planned to be completed in 2024.

**Conclusions:**

The presented paper describes Happy Smiles, a project that provides an opportunity to address the aesthetic inconvenience of patients without compromising the effectiveness of the SDF treatment. The trial findings will contribute to the limited evidence base related to discoloration after SDF intervention to improve aesthetic appearances in child oral health. If the results from the trial are promising, it will lead to the development of a model for child oral health and pave the way for further research in child oral health.

**International Registered Report Identifier (IRRID):**

PRR1-10.2196/51087

## Introduction

Developments in our understanding of the pathophysiological processes underlying dental caries led to the development of minimal intervention dentistry, which emphasizes the critical importance of maintaining the integrity of the natural tooth structure and adopts a biological approach in the management of caries lesions [1,2]. Nishino et al [3] described the caries-arresting properties of silver diamine fluoride (SDF) in 1969. SDF is a colorless liquid substance with a pH of 10 that contains 5% to 5.9% fluoride and 24.4% to 28.8% (weight by volume) of silver [4]. The primary reason for SDF’s efficacy in preventing caries is its microbicidal impact on cariogenic biofilm [5,6]. SDF treatment results in a decrease in size and an increase in mineral density and hardness in carious lesions [7].

Children, hospitalized patients, people with mental disorders, people who have received radiation and chemotherapy, and patients with xerostomia, as well as all those with high rates of tooth decay, can benefit from SDF [8]. This is a therapy option in dental clinics and community dental health initiatives due to its low cost and the simplicity of its application. A significant service that dental auxiliaries can be trained to provide is stopping active caries [9]. SDF should be applied every 6 months and no more than 3 weeks apart [10].

Despite the strong evidence for SDF’s antibacterial effectiveness in arresting tooth caries, its clinical application has been relatively limited until now [11]. Location and tooth type have a major impact on parental acceptance of SDF therapy. Parental acceptability of SDF treatment is considerably greater for primary teeth than permanent teeth, and for posterior teeth than anterior teeth in both dentitions [12]. Regardless of the type and location of the teeth, parents of children who had previously exhibited resistant behavior during dental treatment were significantly more receptive of SDF treatment than parents of cooperative children [12].

Contrary to anterior teeth, posterior tooth staining is more widely accepted. Even though anterior tooth discoloration is undesirable, parents prefer SDF treatment to any other complex behavioral approaches like sedation or general anesthesia, which are not appreciated by most parents [13]. The precipitation of silver phosphate is what causes the discoloration that occurs after applying SDF (which has the formula Ag_3_PO_4_) [14].

In order to overcome this problem and increase the clinical use of SDF, a new method of application has been suggested [15]. This includes treating the initial layer of SDF with a layer of potassium iodide (KI), which combines with the free silver ions in SDF and inhibits the precipitation of silver phosphate. Since then, numerous investigations have shown that using KI after SDF creates a yellow silver iodide precipitate and prevents tooth stains from turning dark [10,16]. Following the application of KI in a dose-dependent manner, Detsomboonrat et al [17] noticed a considerable and immediate reduction in staining caused by SDF.

Studies demonstrating that KI reduces black staining are still insufficient. This paper presents the study protocol for Healthy Smiles, a randomized controlled trial implemented to compare the staining propensity of SDF+KI.

The aim of the study is to evaluate the staining propensity of SDF+KI among children aged 4 to 6 years by incorporating artificial intelligence in dentistry as a tool for precise interpretation of the findings, which will add to the evidence pool. The objectives of the study include (1) to evaluate the staining propensity of SDF+KI using a Nix Mini color sensor (Nix Sensor Ltd) among children aged 4 to 6 years, (2) to evaluate the caries-arresting effect of SDF+KI in the treatment of carious primary teeth, and (3) to assess parental satisfaction with dental appearance and color following treatment with SDF versus SDF+KI using a detailed questionnaire (Table 1). We hypothesized that there would be no difference in the staining propensity of SDF+KI among the children.

**Table 1 table1:** Objectives and measures.

Objectives	Measures	Description
1. To evaluate the staining propensity of SDF^a^ and SDF plus KI^b^ using the Nix Mini color sensor among children aged 4 to 6 years.	Child dental examination	At the end of 1, 3, and 6 months after treatment each tooth will be photographed and each tooth’s color change will be measured using the Nix Mini color sensor.
2. To evaluate the caries-arresting effect of SDF and SDF+KI in the treatment of carious primary teeth.	Arrest of carious lesions (6 and 12 months after treatment)	The progression in the size of the carious lesions will be evaluated using the ICDAS^c^ index as stable or progressing. The consistency of the lesions will be evaluated upon gentle probing using a ball-ended World Health Organization probe as soft or hard carious lesions.
3. To assess parental satisfaction with dental appearance and color following treatment with SDF and SDF+KI.	Parental questionnaire using prevalidated 5 point-Likert scale (immediately after treatment)	“You are satisfied with your child's aesthetics after SDF/SDF+KI treatment.” “SDF/SDF+KI application is an easy process.” “SDF/SDF+KI application is pain free for your child.” “SDFSDF+KI taste is acceptable to your child.”

^a^SDF: silver diamine fluoride.

^b^KI: potassium iodide.

^c^ICDAS: International Caries Detection and Assessment System,

## Methods

### Study Design

Healthy Smiles will be carried out for a period of 1 year. The study is an active-controlled, parallel-group randomized controlled trial. A detailed schedule of enrollment, interventions, and assessments is given as a SPIRIT (Standard Protocol Items: Recommendations for Interventional Trials) schedule (Figure 1).

Baseline data will be collected and the children will receive the intervention. The examination will be done by a single examiner with the help of recorders from government-run nonformal preschools and primary schools in Mangaluru, India. This schedule is designed with slight flexibility in order to accommodate any unforeseen lapses or inconveniences. This trial has 3 phases, including data collection, intervention, and follow-up (Figure 2).

**Figure 1 figure1:**
[figure not shown]
SPIRIT (Standard Protocol Items: Recommendations for Interventional Trials) schedule of enrollment, interventions, and assessments. ICDAS: International Caries Detection and Assessment System; KI: potassium iodide; SDF: silver diamine fluoride; t0: baseline; t1-t4: 1-, 3-, 6-, and 12-month follow-ups.

**Figure 2 figure2:**
[figure not shown]
Phases of Healthy Smiles. CPI: Community Periodontal Index; ICDAS: International Caries Detection and Assessment System.

### Study Location

The study will be conducted in primary schools and government-run nonformal preschools in Mangaluru, India. Inclusion and exclusion criteria are shown in Textbox 1.

Inclusion and exclusion criteria.
**Inclusion criteria**
Children aged from 4 to 6 yearsChildren who meet the criteria for International Caries Detection and Assessment System (ICDAS) code 1 or greaterChildren who have one or more active carious lesions in primary teeth not involving the pulpParents who give consent for participation in the study
**Exclusion criteria**
Children with preshedding tooth mobilityChildren with signs of pulpal or periapical infectionChildren with gingival or perioral ulceration or stomatitisChildren who have any history of allergies

### Recruitment: Trial Participants

A total of 120 children will be examined in the government-run nonformal preschools and primary schools by the supervising staff (guide) and the primary investigator. The sample size will be 60 children.

### Randomization

The names of 60 children will be selected randomly with a computer-generated table of random numbers by an independent assistant using the Stat Trek (StatTrek.com) random number generator. The names will be randomly distributed into 2 groups (SDF and SDF+KI) with a lottery method for the next phase. For the trial, 2 groups will be assigned: group 1 and group 2. The assistant, who is independent of the trial, will be responsible for giving each child a serial number indicating his or her allocation. Blinding of the examiner or the children will be impossible during the intervention and follow-up due to the different natures of the materials. However, the assistant, who will be responsible for giving and collecting the questionnaires from the parents or guardians, as well as the statistician, will not know the group to which the child belonged.

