### Statistical Power

The sample size was calculated with G*Power (version 3; Universität Düsseldorf). Based on the results of Aly and Yousry [18], at a 5% level of significance and 95% power with an effect size of 1.594, (calculated by considering that the mean lightness value of one group was 71.3, SD 14.2 and the other group was 53.6, SD 6.7), and the primary end point being an evaluation of the staining propensity of SDF+KI at the end of 1, 3, and 6 months after treatment, with a 95% chance of detecting an increase in the mean lightness value from 53.6 in the control group to 71.3 in the experimental group, the minimum sample size in each group is 16. The expected dropout rate is 10%, so after considering the dropout rate, the sample size in each group is 30. Thus, the total sample required for the intervention will be 60 children (N=60).

For the secondary objective, with a significance level of 5%, a power of 80%, and an estimated critical *Z* value of 3.193, the study required 48 teeth, or 24 teeth per group. Finally, assuming 40% loss to follow-up, a sample size of 34 teeth was gathered in each group [19] to evaluate the caries-arresting effect of SDF+KI in the treatment of carious primary teeth at 6 and 12 months after treatment.

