#### Clinical Examinations

Clinical examinations will be performed by visual inspection under visible light, with the children in an upright position. The children will be assessed for dental caries using ICDAS codes and criteria. ICDAS codes 0-3 can be determined with air drying. Using a ball-ended World Health Organization (WHO) Community Periodontal Index probe, cavitated lesions (ICDAS codes 5 and 6) will be probed.

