### Data Analysis

Data will be analyzed using SPSS (version 28; IBM Corp). Descriptive statistics will include the mean and SD for continuous data and frequency and percentage for categorical data. An independent-sample 1-tailed *t* test or the Mann-Whitney *U* test will be used for comparing the 2 groups. *P* values will be considered statistically significant at ≤.05.

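### Sixty children are split by one unstratified lottery and compared without adjustment, although the article calls tooth location a major influence on parental acceptance

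*Protocol article*

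**What the plan says.** All places are in the protocol article.

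- **Eligibility (Textbox 1).** Children aged 4 to 6 qualify with at least one active primary-tooth lesion that spares the pulp, at ICDAS 1 or higher. Infection of the pulp or around the root excludes a child. No tooth position is excluded and no upper ICDAS code is set.
- **Severity range (Clinical Examinations).** Advanced lesions are expected: "cavitated lesions (ICDAS codes 5 and 6) will be probed".
- **Allocation (Randomization).** "The names will be randomly distributed into 2 groups (SDF and SDF+KI) with a lottery method for the next phase". No strata, blocks or minimisation are named. Statistical Power gives 30 children per group, 60 in all.
- **Analysis (Data Analysis).** "An independent-sample 1-tailed *t* test or the Mann-Whitney *U* test will be used for comparing the 2 groups". No covariate is named.
- **Rationale (Introduction).** "Location and tooth type have a major impact on parental acceptance of SDF therapy". The same section says that posterior teeth are better accepted than anterior teeth.
- **Outcomes (Table 1, Phase 3).** Colour change is primary. Arrest, scored by ICDAS progression and lesion consistency, and parental satisfaction are secondary. One of the four satisfaction items concerns aesthetics. The others cover ease, pain and taste.

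**The concern.** The article names tooth location as a strong influence on how parents judge the treatment, then asks parents to judge its appearance, and controls location neither in the draw nor in the stated comparison. If chance gives one arm more anterior lesions, a satisfaction difference could partly reflect where the teeth are rather than whether KI was added. Lesion severity raises a similar question for arrest, because that outcome is itself scored by ICDAS progression and by soft or hard consistency. With 30 children per arm, such gaps are not rare.

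**Working it through.** **Inputs from the article.** 60 children, 30 per arm; "at a 5% level of significance and 95% power with an effect size of 1.594"; "the mean lightness value of one group was 71.3, SD 14.2 and the other group was 53.6, SD 6.7".

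**Assumed, because the article gives no figure.** The share of children with the factor (for example an anterior lesion) is 20% to 50%; shares above 50% mirror those below. The factor's effect on an outcome is 0.5 or 1 SD. Two factors are independent.

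**1. The plan's own figure.** Pooled SD = √((14.2² + 6.7²)/2) = 11.10. Effect size = (71.3 − 53.6)/11.10 = 17.7/11.10 = 1.594, as stated. How the article gets from this to 30 per group is a separate matter; 30 is taken as given here.

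**2. Chance of imbalance.** If K of the 60 children carry the factor and 30 are drawn for one arm, the number X in that arm is hypergeometric (60, K, 30). The gap between arms is |2X − K|/30, so 20 points means a difference of at least 6 children, for example 18 against 12. For two independent factors of equal prevalence, the chance that at least one is this unbalanced is 1 − (1 − p)².

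| Assumed share | K | p: gap ≥ 20 points | Gap ≥ 30 points | At least one of two factors ≥ 20 points |
|---|---|---|---|---|
| 20% | 12 | 0.104 | 0.002 | 1 − 0.896² = 0.197 |
| 30% | 18 | 0.158 | 0.010 | 1 − 0.842² = 0.291 |
| 40% | 24 | 0.187 | 0.017 | 1 − 0.813² = 0.339 |
| 50% | 30 | 0.196 | 0.019 | 1 − 0.804² = 0.354 |

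**3. Consequence for satisfaction.** A factor worth g SD with a gap D shifts the contrast by gD SD. With 30 per arm the standard error is 1/√15 SD, so the test statistic moves by gD√15. For the one-tailed 5% test (normal approximation), given D = 0.20 in the direction of the tested alternative:

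- g = 1: shift 0.20 SD; 0.20 × 3.873 = 0.775; false-positive rate 1 − Φ(1.645 − 0.775) = 0.19.
- g = 0.5: shift 0.10 SD; 0.10 × 3.873 = 0.387; false-positive rate 1 − Φ(1.645 − 0.387) = 0.10.

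These rates are conditional on an imbalance in one direction, which has about half the tabulated probability (0.104/2 = 0.05 to 0.196/2 = 0.10). In the other direction with g = 1, the rate falls to 1 − Φ(1.645 + 0.775) ≈ 0.01.

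**4. Consequence for staining.** A factor worth a full SD (11.1 L units, assumed) shifts the contrast by 0.20 × 11.1 = 2.2 units at a 20-point gap and 0.30 × 11.1 = 3.3 units at a 30-point gap. Against 17.7 units that is 2.2/17.7 = 12% and 3.3/17.7 = 19%. If the whole shift acts against KI, 15.5 or 14.4 units remain, and power at 30 per group stays above 99.8%, one- or two-sided.

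**The case against.** The strongest reply is that simple randomisation is sound. Chance imbalance is already part of the sampling distribution behind the test, so the overall type I error holds and there is no systematic bias. That stands: the point concerns precision and robustness, and no error in the design is shown.

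Several further replies also have weight:

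- **Staining.** A reader might infer that the primary outcome is at risk. The article does not support this. It ties location to parental acceptance, and nowhere says that position or ICDAS code changes ∆L or ∆E. Step 4 shows that even a large assumed effect would be minor against the planned difference.
- **Satisfaction.** Acceptance of SDF therapy is related to satisfaction after treatment but is not the same thing, and only one of four items asks about appearance. The 19% needs an assumed 1 SD effect and an imbalance in one direction.
- **Severity.** A reader might take eligibility to cover every lesion from ICDAS 1 to 6. The requirements that lesions be active and spare the pulp, and the exclusion of infection, narrow it, although codes 5 and 6 are plainly expected.
- **Adjustment.** Covariates may be set out in an analysis plan that is not shown. If so, that half of the point falls away. Stratification does not depend on that plan: it must be settled at allocation, and the article describes a plain draw.
- **Several lesions.** A child with both anterior and posterior lesions has no defined stratum, so stratifying needs one extra rule.

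**Conclusion.** The point holds as a cheap improvement to a valid design. An unstratified 30/30 draw has about a 10% to 20% chance of leaving the arms at least 20 points apart on tooth position, and about a 20% to 35% chance of doing so on at least one of position and severity. These figures rest on assumed prevalences of 20% to 50% and, for the pair, on independence. Gaps of 30 points or more are rare, at 0.2% to 1.9%. The satisfaction contrast, through its aesthetics item, has the clearest exposure, because the article itself names location as influential. Arrest is a possible second. The documents support neither a claim that the trial is biased nor a claim that the staining comparison is in danger.

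**What to change.** **If allocation is not complete.** State a rule that names one index lesion per child at the baseline examination. The independent assistant then runs the lottery separately for children with an anterior and a posterior index lesion and, if counts allow, within ICDAS 1–4 and 5–6, the cut that Clinical Examinations already uses for cavitated lesions. The index lesion defines the stratum only; it need not limit which teeth are assessed.

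**In any case.** Replace the unadjusted comparisons with ones adjusted for baseline position and ICDAS group: for example, linear regression for colour change, ordinal regression for satisfaction items and logistic regression for arrest. Enrollment began in October 2023 according to Results, so allocation may already be done. If so, keep it and use the adjustment alone.

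**Cost.** One index-lesion rule, two or four draws instead of one, and one or two degrees of freedom. Strata with odd counts may leave each arm a child or two away from 30. No extra children or visits are needed: severity is coded at the baseline examination, and position follows from which tooth is coded.

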#### Method of Application

In group 1, we will use cotton gauze to carefully clean and dry the affected tooth surface. The gingival tissue of the tooth will be protected with petroleum jelly. An applicator will be dipped into the SDF and 2-3 mg will be applied to the lesion with a microbrush, which will be used to paint the solution over the carious lesion; then, we will wait for 1 minute for absorption.

In group 2, we will apply SDF with the same technique. After the SDF application, KI will be applied using a separate microbrush, which will be saturated with the solution and will be used to paint the solution over the carious lesion. No rinse will be performed and special instructions will be given following application.

After treatment, an individual report on the child’s oral health will be provided, and after-treatment instructions will be given to the parents. If there is any adverse drug reaction associated with the SDF treatment, the parents will be asked to contact the principal investigator immediately by telephone.

All teeth will be photographed immediately after treatment. A high resolution mobile camera will be used to capture all of the images throughout the study. The high-resolution mobile camera features a 64-megapixel primary camera with an 8-megapixel secondary depth camera and an 8× optical zoom to provide images at a 2340×1080-pixel resolution.

Each tooth’s color will be measured using a Nix Mini color sensor. The Nix Mini color sensor is a wireless colorimeter that uses artificial intelligence to measure the exact color of surfaces and transmits the digital color values to a smartphone or tablet using Bluetooth.

Measurements will be calibrated in accordance with the manufacturer’s instructions to determine the first shade of the carious lesion. The ∆L and ∆E values will be measured 3 times by a single operator, and the average values will be noted. Despite the fact that SDF treatment had no adverse effects in other studies, if any adverse events occur, the primary investigator will duly report them to the institutional ethics committee.

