## Results

Enrollment started in October 2023. It is estimated that the enrollment period will be 12 months. Data collection is planned to be completed in 2024.

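### The single lottery does not fit the 12-month enrolment, and the colour reference is read after allocation is known and apparently after treatment

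*Protocol article*

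**What the plan says.** **Allocation.** Under Recruitment, "A total of 120 children will be examined" for a sample of 60. Under Randomization, "The names of 60 children will be selected randomly with a computer-generated table of random numbers by an independent assistant", and then "The names will be randomly distributed into 2 groups (SDF and SDF+KI) with a lottery method for the next phase". The same assistant "will be responsible for giving each child a serial number indicating his or her allocation".

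**Calendar.** The Results section states: "Enrollment started in October 2023". It continues: "It is estimated that the enrollment period will be 12 months". It plans for data collection to end in 2024. Study Design gives the trial a duration of 1 year. Staining is assessed at 1, 3 and 6 months after treatment, and caries arrest at 6 and 12 months.

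**Colour.** Phase 1 lists sociodemographic details and the ICDAS examination, with no colour reading. The sensor enters in Phase 2, Method of Application, after the application steps, where it is calibrated "to determine the first shade of the carious lesion". The Discussion (Principal Findings) gives the only explicit timing for its first use, straight after treatment, and says that ΔL and ΔE will be compared between the groups.

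**Masking.** "Blinding of the examiner or the children will be impossible during the intervention and follow-up". Only the assistant who handles the questionnaires and the statistician are said not to know the group.

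**The concern.** Two steps are fixed in an order that either clashes with other statements or weakens the primary outcome.

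First, a random selection of 60 names followed by a lottery over those names presupposes a closed list. A 12-month enrolment suggests that children come in over time. The article does not say which of these governs, and each has consequences for the age of the baseline data and for how allocation is actually made.

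Second, ΔL and ΔE are changes from a reference reading. If an operator who knows the arm takes that reading, the placement of the sensor on the lesion can be influenced. If it is taken after SDF or SDF+KI has been applied, the reference already contains part of the treatment effect, and the change score removes that part from the comparison. A serial number that shows the arm makes the first problem harder to contain.

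**Working it through.** **1. The number of names.** The planned effect size reproduces: (71.3 − 53.6) / √((14.2² + 6.7²)/2) = 17.7 / 11.10 = 1.594. The step from 16 per group to 30 does not follow from 10% dropout, since 16/0.90 = 17.8, or 18. That is a separate matter. Here 60 is only the number of names in the lottery, and nothing below depends on how it was derived.

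**2. Calendar.** Inputs: start October 2023, enrolment 12 months, last colour visit 6 months, last arrest visit 12 months.
- End of enrolment: October 2023 + 12 months = about September/October 2024.
- *One draw after the last child is examined.* Treatment starts about October 2024. The earliest ICDAS record is then up to 12 months old. The 6-month reading falls about March/April 2025 and the 12-month visit about September/October 2025. Total length is 12 + 6 = 18 months for colour and 12 + 12 = 24 months for arrest, against a stated 1 year.
- *Treatment on arrival.* The last child has the same visit dates. To be seen by December 2024, a child must be treated by June 2024 for the 6-month visit and by December 2023 for the 12-month visit. A random selection of 60 names from a closed list, followed by one lottery, would not have taken place.

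Completion in 2024 fails on either reading. The lottery as described survives only on the first.

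**3. Order of the colour reading.** The sections side by side:
- Phase 1: ICDAS and sociodemographic data only.
- Lottery: assigns children for the phase that follows.
- Phase 2: application, then photographs, then sensor.
- Discussion: sensor used straight after treatment.

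The first reading therefore follows the lottery and, by the only timing stated, follows application. One operator takes it and is not among those described as unaware of the group.

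**4. What a post-treatment reference does to ΔL.** For mean lightness, the arm difference in ΔL equals the arm difference at follow-up minus the arm difference at the reference. Before treatment the second term is zero in expectation. After treatment it is the immediate effect; the Introduction cites a study in which KI reduced SDF staining at once. Suppose a share f of the planned 17.7-point difference is present at the reference (assumed, f between 0 and 1). The ΔL contrast is then 17.7 × (1 − f):
- f = 0: 17.7
- f = 0.5: 8.85
- f = 1: 0

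The article gives no basis for choosing f. A comparison of lightness itself at follow-up, which is how the sample size is framed, would not be affected in this way.

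**5. Chance imbalance in severity.** Let K of the 60 children be in the more severe group (assumed, as no distribution is given) and X of these be drawn into one arm of 30. X is hypergeometric(60, K, 30), and the gap in proportions is |2X − K|/30. A gap of 20 points or more means |2X − K| ≥ 6.
- K = 15: 7.2% (|2X − K| is odd here, so at least 7 is needed)
- K = 20: 17.0%
- K = 30: 19.6%

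**The case against.** Several objections are sound and limit the point.

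- *The lottery is feasible.* A reader might infer that it cannot be run at all. The article does not support that: examining 120 children, drawing 60 and splitting them once is a coherent procedure, and enrolment is not defined. Screening and draw could even be completed early, with the 12 months covering treatment. But allocation would then be known, and ICDAS would have aged, for up to 12 months before the last children are treated. What stands is a conflict to reconcile.
- *Choice of lesion.* Children may have several lesions, so a reader might infer that the lesion to be measured can be picked with the arm known. Table 1 and Method of Application have every tooth measured, which largely answers this. Only the spot within the lesion is left open. Averaging three readings reduces random error but does not prevent a systematic choice of spot.
- *Timing.* The phrase about the first shade may mean a pre-treatment reading, and the schedule in Figure 1, which has a baseline column, is not shown. Even so, the text places that reading in Phase 2, after the lottery. The cause is the position of the reading, not the lottery itself.
- *Severity.* A reader might infer that severity will be, or is likely to be, unbalanced. Randomisation balances it in expectation, and a gap of 20 points or more is absent in at least 80% of draws under the assumptions used. A condensed article may also leave strata and blocks to the full protocol, so their absence is no defect.

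**Conclusion.** The point holds in two parts. The single draw over a closed list conflicts with the stated enrolment period and with completion in 2024: follow-up of the last child reaches about March/April 2025 for colour and September/October 2025 for arrest. The reference for ΔL and ΔE is read after allocation by an unblinded team that holds an arm-revealing number and, by the only timing given, after application.

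The calendar result needs only the article's own dates. The size of the bias in ΔL cannot be derived. The range from 17.7 down to 0 rests on an assumed share of the effect being present at the reference, and it disappears if the reading is in fact taken before treatment. Even then the reading would follow the lottery. Severity imbalance is a chance risk of about 7% to 20% for a 20-point gap if 15 to 30 children are in the more severe group. It supports an optional improvement and is not part of the defect. The change should be made, because it removes an avoidable source of bias in the primary outcome at little cost.

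**What to change.** 1. Reconcile the draw with the enrolment period and the 2024 completion date. One workable form is to draw per batch, for instance per school visit, once every child in the batch is consented and examined.
2. In Phase 1, for every study tooth, fix and record the measuring spot and take the reference sensor reading before the draw and before treatment. State that ΔL and ΔE are calculated from this reading. Any reading straight after treatment becomes a follow-up value.
3. Give each child a neutral serial number and keep the allocation list separately with the independent assistant. If this is also the assistant who handles the questionnaires, the statement that this person does not know the group has to be reconciled with issuing the allocations.
4. Optionally, stratify the draw by ICDAS group (codes 1-3 and 4-6, by the child's most severe study lesion). Odd allocations must be carried across batches; halving within each small batch alone does not keep the arms within one or two children of each other.

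Cost: some reordering of visits, slightly more work for the assistant and, if the reading straight after treatment is kept, one additional sensor measurement per tooth. No extra staff or equipment is needed.
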